### Inclusion and exclusion criteria

Patients aged between 18 and 65 with primary diagnoses of SAD on Axis I and comorbid APD on Axis II will be included in the study. Primary diagnosis is defined as the diagnosis on which treatment should focus at first instance according to both patient and clinical staff. Other inclusion criteria are willingness, motivation and practical ability to attend 30 sessions of group therapy and to refrain from treatment or counselling outside the context of the present trial. The use of antidepressant medication or benzodiazepine will be permitted, under the condition that the medication dose has been stable for at least 3 months before inclusion and patients are willing not to raise the dosage of the medication during the active phase of the trial. Furthermore, patients must be willing to complete homework assignments between sessions and must sign written informed consent to participate in the study.

Exclusion criteria are suicidality and the presence of psychotic or bipolar symptoms, because these conditions could interfere with the measurement and treatment procedures and suggest an immediate need for alternative interventions. Another exclusion criterion is an Axis I diagnosis of substance abuse or dependence which needs, according to the clinical staff, detoxification (after successful detoxification patients can participate). Moreover, patients with a primary Axis II diagnosis of a borderline, antisocial, schizoid, schizotypal personality disorder will be excluded, because they need highly specialized treatment. Patients in whom there is a suspicion of an autism spectrum disorder (based on a sum score on the Autism-Spectrum Quotient (AQ) higher than 32) [27], who have an IQ less than 80 (in case of suspicion an intelligence test is taken), and problems with the Dutch language (talking, reading, writing) will also be excluded.

### Inclusion and exclusion procedure and randomization

Patients who are registered for treatment at the department of anxiety disorders will be screened on the presence of Axis I disorders by the intake clinician. Eligible patients are patients diagnosed with SAD, or in the case of more than one Axis I diagnosis (e.g. panic disorder or depressive disorder), patients for whom social anxiety should be the principal focus of treatment, according to both patient and clinical staff. At first instance these patients will receive concise information about the study by the intake clinician. At PsyQ The Hague they will then receive a leaflet containing information about the study, which is sent by mail after a research assistant has informed the patient by phone. At PsyQ Rotterdam the leaflet is handed over at the first appointment by the intake clinician or during a second appointment in which the patient is given treatment advice. Patients of that location will be contacted by the research staff after the Axis II diagnosis of APD is established.

Eligible patients are invited for a diagnostic interview — consisting of the Structured Clinical Interview for DSM-IV Axis II Personality Disorders (SCID-II) — to determine the presence of Axis II disorders and other inclusion and exclusion criteria. Beforehand patients receive the AQ and the pre-screener of the SCID-II. During the SCID-II interview all cluster C personality disorders are fully investigated. All confirmatively answered and all unanswered questions on the pre-screener will also be assessed with the SCID-II interview. If the personality trait is confirmed and the amount of confirmed traits pertaining to a certain personality disorder exceeds three, all traits pertaining to that personality disorder will be assessed with the SCID-II interview. Besides scores on the pre-screener, clinical judgement can also be a reason to fully examine a certain personality disorder. In addition to SCID-II, the Mini-International Neuropsychiatric Interview (MINI), section social anxiety, is also administered. The MINI interview is part of the intake procedure of both anxiety departments of PsyQ in addition to a general clinical interview. Some of the patients entering this study will have recently signed up for treatment and will have completed this procedure, but referral by other departments or during ongoing treatment is also possible. It was therefore decided to add the SAD section of the MINI to ensure that patients included meet the inclusion criteria of both SAD and APD.

During the examination, patients will receive additional verbal and extensive written information about the study with respect to both treatment conditions and consequences of participating. After conclusion of the SCID-II administration, patients will be either informed directly or receive a follow-up appointment to discuss the findings of the interview. Patients will have 2 weeks to consider participation, after which they will be contacted by a research assistant. Written informed consent will be obtained from patients who are willing to participate, and they will be asked to fill in the baseline assessment comprising different self-report questionnaires. To be able to assess the frequency and severity of manifestations of APD, a semi-structured interview was developed: the AVPDSI. The AVPDSI interview is administered by phone by a trained psychologist or a trained master student in clinical psychology who fulfils a traineeship at the PsyQ anxiety department.

After a final file check of inclusion and exclusion criteria based on the patient file and after all baseline measures are completed, a research assistant will randomize the patients to the GCBT or GST condition using a computer-generated list (https://www.random.org/lists/). Patients will be randomized in pairs or multiples of pairs. In case of uneven dropout from treatments, a weighted randomization will be done to prevent one of the groups from becoming too small. For both locations this will be done separately.

The main researchers and other outcome adjudicators are blind to group assignment to protect integrity of data collection and analysis. Because it is impossible for a therapist to offer and for a patient to receive therapy without being aware of the techniques they are using or receiving, therapists and patients are not blind. Finally, because data collectors are also employed as therapists in the anxiety departments of the participating sites, they are able to access patient records. Therefore, data collection of clinician-administered measures cannot be blinded. To reduce the risk of biased data collection, therapists involved in delivering either the GCBT or GST are not involved in data collection.

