### Population/sample size

Before the start of the randomized controlled trial (RCT), a chart review showed that both the PsyQ location of Rotterdam and the PsyQ location of The Hague have an annual patient flow of 40 patients with both SAD as well as a comorbid APD. This represents an overall yearly *N* of 80, of which it is expected that approximately 90 % (*N* = 72) will be included. This means that every year in each department 36 patients can be randomized over the two conditions. CBT and ST groups consist of a maximum of 9 patients.

We know that CBT has a large effect on SAD compared to waitlist and a small to moderate effect compared to placebo [15]. With respect to ST, in a randomized trial comparing ST, clarification therapy and treatment as usual (TAU), Bamelis et al. [19] found an odds ratio between ST and TAU in recovery from PD diagnosis in the 3–4 range (depending on the specific (sensitivity) analysis), which is equivalent to Cohen’s *d* = .60–.76 [26]. Though a substantial number of patients in the ST condition had a diagnosis of APD, only a small minority of patients received CBT as TAU. No studies are available directly comparing ST with CBT with respect to APD with comorbid SAD. We therefore designed our RCT as a superiority trial with enough statistical power to detect a difference in outcome between treatments (if present) with a medium effect size (Cohen’s *d* = .5). We chose this minimum difference because such a difference is important based on a patient’s perspective or clinical knowledge. Expecting larger differences in outcome does not seem realistic and might result in an underpowered study, while detecting smaller differences is of less relevance for clinical practice. Thus, we designed our study to detect a medium effect size (0.50) with a power of 80 % and a two-tailed alpha set at 0.05 on the primary outcome measures, severity of social anxiety (Liebowitz Social Anxiety Scale Self-Report, LSAS-SR) and severity of avoidant personality disorder (Avoidant Personality Disorder Severity Index, AVPDSI). This implies that 64 patients per study group and in total 128 patients are needed for the present project.

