### Dropout and follow-up

In case of emergencies (like severe increase of symptoms, suicidality) deviation from the protocol is allowed. Subjects can leave the study at any time for any reason if they wish to do so. The researcher can — in consultation with the group therapists — also decide to withdraw a subject from the study for urgent medical or psychological reasons. Reasons for dropout or withdrawal will be registered. Patients who withdraw from treatment will also be asked to complete follow-up assessments. As mentioned before, during the active treatment phase, participation in other treatments, starting medication or raising the medication dosage is not allowed. Also missing too many sessions is not permitted (patients should at least attend a minimum of 80 % of the sessions); if too many are missed, treatment will be terminated (pushout). In consultation with the patient, taking into account the reason for dropout, a suitable alternative will be discussed.

The follow-up period is experimental for the first 3 months (patients are not provided additional treatment unless clinically deemed necessary, e.g. in case of crisis). After this period, patients are offered an appointment with one of the group therapists. Depending on the wish of the patient, main treatment results and further treatment needs can be discussed. From then on follow-up will be naturalistic, meaning that patients are free to seek help in case of unsatisfactory treatment results and/or additional need for treatment.

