### Statistical analysis

Pre-test differences between both treatment groups and between treatment completers and dropouts will be calculated by means of independent *t* tests, nonparametric tests or chi-square tests when appropriate. Multilevel analysis (MLA) will be used to investigate the effectiveness of GCBT and GST in reducing social anxiety symptoms and manifestations of AVPD, and the secondary outcomes. MLA is especially suitable to analyse repeated measure data because it takes into account the dependencies among observations nested within individuals. Another advantage of this methodology is its ability to handle missing data, a problem often occurring in longitudinal research [66]. The data has a three-level hierarchical (multilevel) structure: repeated measures at the first level, individuals at the second level, treatment condition at the third level. For dimensional outcomes the appropriate underlying distribution (e.g. normal, gamma, negative binomial) will be determined based on the observed distributions of residuals. For the repeated part, the best fitting covariance structure will be determined empirically. Moreover, multilevel logistic regression analysis will be performed in order to investigate whether GCBT compared to GST results in a higher proportion of remitted APD. Survival analysis will be used to compare conditions in treatment retention. The identification of possible predictors, moderators and mediators will be based upon the recommendations of Kraemer [25]. Linear regression methods will be applied to identify predictors/moderators related to treatment outcome. Bootstrapping methods [67] will be used to investigate the mediating effects of, for example, emotion regulation on symptom reduction. Furthermore, effect sizes and clinical significant change according to the Jacobson and Truax criteria [68] will be calculated to estimate respectively the magnitude of the treatment effect and the significance of the results for clinical practice.

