### Trial status

The trial was registered on 25 March 2013 in the Dutch Trial Register (NTR3921). Participants are currently being recruited and enrolled. The trial started recruitment in March 2014 at PsyQ The Hague and in May 2015 at PsyQ Rotterdam.

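### The allocation ratio may be changed by site in response to uneven treatment dropout, which can bias an unadjusted comparison and gains nothing for the size of the trial arms

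*Protocol article*

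**What the plan says.** All statements are in the protocol article.

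- Inclusion and exclusion procedure and randomization: allocation starts in balance, "Patients will be randomized in pairs or multiples of pairs". The next sentence makes an exception: "In case of uneven dropout from treatments, a weighted randomization will be done to prevent one of the groups from becoming too small". Then: "For both locations this will be done separately". The article does not say how uneven dropout must be, what weight applies, when weighting stops or who decides.
- Population/sample size: the trial is designed to "detect a medium effect size (0.50) with a power of 80 % and a two-tailed alpha set at 0.05". "This implies that 64 patients per study group and in total 128 patients are needed for the present project". The same section uses 'group' both for the study arms and for the therapy groups, which hold at most 9 patients.
- Dropout and follow-up: "Patients who withdraw from treatment will also be asked to complete follow-up assessments".
- Statistical analysis: the multilevel model has repeated measures, individuals and treatment condition as its levels. On incomplete data: "Another advantage of this methodology is its ability to handle missing data, a problem often occurring in longitudinal research". Retention in treatment is itself compared between conditions by survival analysis.
- Trial status: "The trial started recruitment in March 2014 at PsyQ The Hague and in May 2015 at PsyQ Rotterdam".

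**The concern.** The ratio would change on a post-randomisation event that differs between arms and is itself an outcome of the trial. From then on, new patients would go more often to the arm that loses more patients, so that arm would hold a larger share of late enrolees. Because each location is handled separately, the ratio could also differ by site, and the arms would then differ in site mix.

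Neither imbalance matters if outcomes are the same across periods and sites. The article gives reasons why they may not be. The sites opened 14 months apart, their pilot periods differed in length, and patients are informed and approached differently at each. If the between-arm analysis leaves out site and period, any such difference enters the treatment effect.

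Against that risk, the gain needs to be clear. For the number of patients per arm in the analysis, it is not.

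**Working it through.** **Plan's own figure.** Inputs from Population/sample size: d = 0.50, SD = 1, power 80%, two-sided alpha 0.05, 1:1. The two-sample t-test gives 63.77, so 64 per arm; power at 64/64 is 0.801. The stated 128 is reproduced. All dropout rates, weights, switch points, drifts and site differences below are assumptions, because the article gives none.

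**Does weighting help arm size?**

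1. *Dropouts stay in the analysis.* 64/64 remains 64/64, power 0.801. Weighting only unbalances the arms: 56/72 gives 0.795 and 48/80 gives 0.776.
2. *Dropouts are lost completely.* Precision depends on n1·n2/(n1 + n2). Let p1 and p2 be the retained fractions and N = 128.
   - At 1:1 this equals (N/2)·p1·p2/(p1 + p2).
   - Weighting to equalise completers leaves N·p1·p2/(p1 + p2) in each arm. Half of that is again (N/2)·p1·p2/(p1 + p2), so the two are identical.
   - At 10% v 30% dropout, 1:1 leaves 57.6 and 44.8: 57.6 × 44.8/102.4 = 25.2, power 0.7005. Weighting randomises 56 and 72 and leaves 50.4 in each: 50.4 × 50.4/100.8 = 25.2, power 0.7004.
   - At 20% v 40%, power is 0.6393 v 0.6391.

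**Enrolment period.** Take the first 64 patients at 1:1 (32/32) and the last 64 at r:1. Bias of the unadjusted difference = drift × (late share in arm A − late share in arm B), with the same drift in both arms. At 2:1 the late patients split 42.7/21.3, so the arms are 74.7 and 53.3. Late shares are 42.7/74.7 = 57.1% and 21.3/53.3 = 40.0%, a difference of 0.171. Bias is 0.171 × 0.3 = 0.051 SD to 0.171 × 0.5 = 0.086 SD.

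For type I error at 2:1, SE = √(1/74.7 + 1/53.3) = 0.179. Dividing the bias by the SE shifts the test statistic by 0.29 to 0.48, which gives 5.9% to 7.7%.

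| Late ratio | Late shares | Bias, drift 0.3 / 0.5 SD | Type I error |
|---|---|---|---|
| 1.5:1 | 54.5% v 44.4% | 0.030 / 0.051 SD | 5.3% / 5.9% |
| 2:1 | 57.1% v 40.0% | 0.051 / 0.086 SD | 5.9% / 7.7% |
| 3:1 | 60.0% v 33.3% | 0.080 / 0.133 SD | 7.2% / 11.3% |

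**Site.** Take 64 patients per site. With 2:1 at one and 1:1 at the other, the share difference is again 0.171, so a site difference of 0.2 to 0.5 SD gives a bias of 0.034 to 0.086 SD. Opposite weights (2:1 and 1:2) give a share difference of 0.333 and a bias of 0.067 to 0.167 SD.

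**Cost of adjusting.** Stratifying by period, variance = 1/Σ(a·b/(a + b)). At 2:1 this is 1/(32·32/64 + 42.7·21.3/64) = 1/(16 + 14.2) = 0.0331, and power is 0.785 by the normal approximation. The same approximation gives 0.807 at 1:1 throughout. At 1.5:1 it is 0.800 and at 3:1 it is 0.754.

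**The case against.** The strongest reply is that 'groups' may mean the therapy groups. These are semi-open, hold at most 9 patients and take new members every 10 weeks. Both treatments use the group itself, GST through group process and GCBT as an exposure setting. Dropout does empty such groups, and keeping dropouts in the analysis does not refill them. This stands. A reader might infer that the rule addresses a problem that does not exist, but that follows only if 'groups' means trial arms, and the wording leaves it open. The effect on allocation is the same under either meaning.

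Second, the analysis may adjust. The Statistical analysis section is a condensed paragraph that names no covariates. The SAP is not shown and could include site and period; the full protocol could hold the trigger. Allocation stays random within each site and ratio period, so adjustment removes the bias from common drift and from site differences. This also stands, and it makes the bias conditional.

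Third, the illustrated drift is common to both arms. Growing therapist experience with GST alone is a different mechanism. If GST were the topped-up arm, its late share would move from 50% to 57.1% and shift the difference by only 0.071 × 0.3 = 0.021 to 0.071 × 0.5 = 0.036 SD. That would be a treatment effect changing over time, to which the type I error figures do not apply. Both treatments were also piloted beforehand (GST for 18 months in The Hague and 32 in Rotterdam), which limits learning during the trial.

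Two further inferences are not supported. Weighting does not contradict randomising in pairs, because it is written as a conditional exception. Rotterdam's later start does not itself confound, because randomisation is done within location.

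**Conclusion.** The point holds in a limited form. The article permits an open-ended, site-specific change of the allocation ratio driven by a between-arm outcome. The arms would then differ in enrolment period and possibly in site mix, and neither is named in the stated model.

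It would go too far to say that the rule confounds the trial. Bias requires three things together: the rule is triggered, outcomes drift or differ by site, and the analysis omits site and period. Under the assumed 2:1 switch at mid-recruitment with 0.3 to 0.5 SD common drift, the bias is 0.05 to 0.09 SD, that is 0.051/0.50 = 10% to 0.086/0.50 = 17% of the target effect. It is smaller for milder weights and larger for 3:1 or for opposite weights by site, and the article sets no limit on the weight.

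That weighting gains nothing for arm size does not depend on the assumed dropout rates, provided the total stays at 128 and the outcome variance is equal in the arms. The sample size of 128 is correct. That dropouts stay in the analysis is implied by the follow-up request and the choice of model; it is not stated outright.

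**What to change.** 1. State which groups the sentence refers to. If it means the trial arms, delete it and keep 1:1 within site throughout.
2. If it means therapy groups whose viability requires weighting, say so, fix the trigger and the ratio in advance, and log the date of every ratio change at each site.
3. In either case, state that all randomised patients are analysed as allocated.
4. If any weighting is or has been used, include the site by allocation-ratio-period stratum as a fixed effect in every between-arm analysis, including retention.

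The cost is a short amendment and one model term. If 1:1 is kept, some therapy groups may run smaller after dropouts. If weighting is used with adjustment, power falls slightly (about 0.785 v 0.807 in the 2:1 example).

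### Patients are randomised separately by site, but site has no place in the stated multilevel structure, and the only stated handling of baseline differences is significance testing between randomised arms

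*Protocol article*

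**What the plan says.** Under Inclusion and exclusion procedure and randomization, the article states: "Patients will be randomized in pairs or multiples of pairs". It adds that weighted randomisation will be used if dropout from the two treatments is uneven, and then: "For both locations this will be done separately".

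The Statistical analysis section describes a three-level structure, with repeated measures within individuals and treatment condition as the top level. Site is not mentioned. On baseline it plans significance tests, parametric or not as the data require: "Pre-test differences between both treatment groups and between treatment completers and dropouts will be calculated by means of independent". No baseline covariate is named. The Design section lists T0 among the repeated measurements, but the article does not say what role T0 plays in the model.

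The sites do not run in parallel. Trial status reports: "The trial started recruitment in March 2014 at PsyQ The Hague and in May 2015 at PsyQ Rotterdam". The Interventions section gives pilot periods of 18 months (GST) and 10 months (GCBT) in The Hague, against 32 and 24 months in Rotterdam, where there was a major reorganisation.

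**The concern.** A factor that restricts the randomisation belongs in the analysis. If site is related to outcome and allocation is balanced within site, an analysis without site overstates the standard error. If allocation is not balanced to the same ratio at each site, the pooled arm contrast also absorbs part of the site difference. The second case is possible here, because weighting is triggered by dropout and applied location by location.

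The stated structure gives its top level to treatment condition. That is a two-category fixed effect and not a sampled level.

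Between properly randomised arms, any baseline difference is due to chance, so a p-value for it answers no useful question. What matters for precision is how the baseline score is used in the outcome model, and the article leaves that open between choices that differ materially in power.

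**Working it through.** **1. The plan's own figure.** Inputs from Population/sample size: d = 0.50 (SD = 1), 80% power, "a two-tailed alpha set at 0.05 on the primary outcome measures". The article concludes: "This implies that 64 patients per study group and in total 128 patients are needed for the present project". The exact two-sample t test gives 64 per arm (power 0.801). The normal approximation gives 63 per arm, and power 0.807 at 64. The stated figure reproduces.

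**2. Omitting site: precision.** Let s be the share of outcome variance due to site (assumed; not in the documents), with balanced allocation within site. The true variance of the contrast is (1 - s) times what the unadjusted model estimates. With n = 64 per arm, the standardised effect is 0.5 × √32 = 2.828. By the normal approximation:

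- true alpha, site ignored: 2[1 - Φ(1.96/√(1 - s))]
- power, site ignored: Φ((2.828 - 1.96)/√(1 - s))
- power, site adjusted: Φ(2.828/√(1 - s) - 1.96)

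| s (assumed) | true alpha, ignored | power, ignored | power, adjusted | loss (points) |
|---|---|---|---|---|
| 0.02 | 0.048 | 0.810 | 0.815 | 0.5 |
| 0.05 | 0.044 | 0.814 | 0.827 | 1.3 |
| 0.10 | 0.039 | 0.820 | 0.846 | 2.6 |

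**3. Omitting site: bias under weighting.** The bias is (p1 - p2) × δ, where p1 and p2 are the shares of each arm that come from the weighted site and δ is the site difference. As an illustration, with every input assumed: 64 patients per site, one site at 1:1 (32/32), the other at 2:1 (42.67/21.33), δ = 0.3 SD.

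- p1 = 42.67/74.67 = 0.571
- p2 = 21.33/53.33 = 0.400
- bias = 0.171 × 0.3 = 0.051 SD, about a tenth of the target effect of 0.50

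If weighting never occurs, or is the same at both sites, the bias is zero.

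**4. How T0 enters the model.** Let r be the baseline-outcome correlation (assumed; not in the documents), and take a two-point contrast with equal variances. With T0 as an unconstrained response and an arm-by-time effect, the variance factor is 2(1 - r). With baseline adjustment it is 1 - r². The ratio is (1 - r²)/[2(1 - r)] = (1 + r)/2. Power uses the t test with effect 0.5/√(factor) and 64 per arm:

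| r (assumed) | 2(1 - r) | 1 - r² | power, unconstrained | power, adjusted |
|---|---|---|---|---|
| 0.4 | 1.20 | 0.84 | 0.727 | 0.865 |
| 0.5 | 1.00 | 0.75 | 0.801 | 0.900 |
| 0.6 | 0.80 | 0.64 | 0.881 | 0.939 |

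If T0 is a covariate, or a response with one common mean for both arms, the model already has about the precision of the adjusted column.

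**The case against.** The strongest reply is that the article describes how the data are nested and does not list fixed effects. Two sites would normally enter as a covariate and not as a level, and covariate lists are commonly left to a full protocol or SAP that is not shown. So a reader might infer that the final model omits site, but the documents do not establish that. What stands against the article is what it does state: a structure whose top level is treatment condition, alongside an allocation scheme run by site.

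A reader might also infer that the baseline tests replace adjustment, or that both arms have free T0 means. Neither is written. T0 is one of the repeated measurements, so the multilevel model may already use it well. The 0.80 to 0.90 gain is therefore conditional on an assumed r, an assumed model and a two-point contrast, whereas the LSAS-SR is measured on six occasions.

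Three further points have force. Randomising in pairs within site largely balances the arms there unless weighting is used. The later start and longer pilots in Rotterdam do not show that outcomes differ, and the gap between the GST and GCBT pilots is 8 months at both sites (18 - 10 and 32 - 24). Finally, the sentence on baseline testing also covers completers against dropouts, a non-randomised comparison where testing is legitimate.

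The sentence on locations could refer to the weighting step alone. That reading does not remove the bias route in step 3 of the working.

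**Conclusion.** The point holds as a weakness in the stated analysis that should be put right. It is not an error that invalidates the trial. Allocation is by site, the stated structure has no place for site, and between-arm baseline tests are planned that can inform nothing.

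The precision cost of omitting site is small, and the error is on the conservative side, under the assumed 2-10% site share. The better reason for including site is validity: site-specific weighting could confound the pooled contrast, by an amount that depends on ratios and a site difference the documents do not give.

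On baseline, the conclusion is conditional. The loss is material if T0 is an unconstrained response (14 power points at r = 0.4, 10 at r = 0.5, 6 at r = 0.6), and nil if it is a covariate or a constrained response. The documents do not support a claim that this loss will in fact occur.

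**What to change.** - Include site as a fixed effect in the between-arm outcome models.
- For continuous outcomes, state that T0 enters either as a covariate or as a response with one common baseline mean for both arms.
- For APD remission and treatment retention, adjust for site, with a baseline severity score such as the AVPDSI as a covariate where sensible. A baseline value of the outcome itself does not serve here: every patient has APD at inclusion, and retention has no baseline score.
- Describe treatment condition as a fixed effect and drop it as a third level.
- Present the between-arm baseline comparison descriptively. Tests of completers against dropouts may stay if wanted.

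The cost is analysis wording only. Site is known, and all baseline measures are completed, before randomisation. Recruitment was still under way when the article was written. No extra patients or visits are needed, and the sample size need not change.
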